**Methods:**

This randomized controlled clinical trial will enroll 66 patients with PD–related constipation and randomly assign them in a 1:1 ratio to the real acupuncture group or the sham acupuncture group. Participants, acupuncturists, outcome assessors, and statisticians will be blinded to group allocation. The 8-week trial consists of a 4-week treatment period followed by a 4-week follow-up period. The primary outcome is the longitudinal change in the Chronic Constipation Severity Score (CCS) over time. Secondary clinical outcomes include weekly complete spontaneous bowel movements (CSBMs), spontaneous bowel movements (SBMs), Bristol Stool Scale (BSS) scores, and Unified Parkinson’s Disease Rating Scale (UPDRS) scores. In addition, exploratory outcomes include levels of short-chain fatty acids (SCFAs), histone deacetylase 1 (HDAC1), and phosphorylated *α*-synuclein at serine 129 (pS129-α-syn) measured in biofluid samples. Adverse events will be systematically monitored throughout the trial. The study is conducted in accordance with the SPIRIT guidelines.

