#### Primary outcome

2.7.1

The Chronic Constipation Severity Score (CCS) was used as the primary outcome measure to quantify constipation severity. The CCS evaluates eight dimensions of constipation, including bowel movement frequency, degree of defecation difficulty, sensation of incomplete evacuation, presence of abdominal pain or bloating, maximum time required for each defecation episode, use of defecation assistance, frequency of unsuccessful defecation urges within 24 h, and duration of constipation. Total scores range from 0 to 30, with higher scores indicating more severe constipation symptoms (Higashimori et al., 2021). To provide a clinically interpretable anchor for treatment response, a reduction of ≥5 points from baseline in the CCS was prespecified as a threshold for clinically meaningful improvement based on previous studies in neurogenic and refractory constipation populations (Kumar et al., 2017; Preziosi et al., 2011). However, we acknowledge that a universally established MCID for PD-related constipation is currently unavailable.

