## Statistical analysis

4

All analyses were conducted according to the intention-to-treat (ITT) principle. The full analysis set (FAS) included all participants who were randomized and received at least one session of treatment. Statistical analyses were performed using SPSS Statistics software (version 26.0). Continuous variables were tested for normality using the Shapiro–Wilk test. Normally distributed data are presented as mean ± standard deviation (SD), whereas non-normally distributed data are expressed as median (interquartile range, IQR). Between-group comparisons were performed using the independent-samples t-test or Mann–Whitney U test, as appropriate. Within-group comparisons were conducted using the paired t-test or Wilcoxon signed-rank test. Categorical variables were analyzed using the Chi-square test. Pearson or Spearman correlation analyses were performed, as appropriate, to evaluate the correlations of SCFAs, HDAC1, and pS129-*α*-syn levels with CCS scores.

Repeated-measures data were analyzed using linear mixed-effects models (LMMs). Fixed effects included group, time, and the group-by-time interaction. Predefined covariates comprised age, sex, disease duration, and levodopa equivalent daily dose (LEDD). Participant-specific random intercepts were included as random effects. The covariance structure for repeated measures was selected based on the Akaike Information Criterion (AIC) and Bayesian Information Criterion (BIC), and the optimal covariance structure was used for model estimation. If the group-by-time interaction was statistically significant, *post hoc* multiple comparisons were performed with Bonferroni correction, and the results were presented as least squares mean differences (LSMDs) with 95% confidence intervals (CIs). Sensitivity analyses, including complete-case analysis and multiple imputation, were conducted to evaluate the impact of missing data on the robustness of the findings. No adjustment for multiple comparisons was applied for exploratory endpoints, including SCFAs, HDAC1, and pS129-*α*-syn; therefore, these findings should be interpreted cautiously pending further validation. All statistical tests were two-sided, and *p* < 0.05 was considered statistically significant.

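### The adjusted between-arm estimates with 95% CIs are planned only when the group-by-time interaction is significant

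*Protocol article*

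**What the plan says.** The abstract defines the primary outcome as a trajectory: "The primary outcome is the longitudinal change in the Chronic Constipation Severity Score (CCS) over time". CCS is measured at baseline, at the end of the 4-week treatment and at week 8, and the main secondary outcomes follow the same visits.

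For repeated-measures data the Statistical analysis section specifies a linear mixed model: "Fixed effects included group, time, and the group-by-time interaction". Age, sex, disease duration and levodopa equivalent dose are covariates. One sentence then deals with estimation. It opens with a condition, "If the group-by-time interaction was statistically significant", goes on to Bonferroni-corrected post hoc comparisons, and ends "and the results were presented as least squares mean differences (LSMDs) with 95% confidence intervals (CIs"). No other sentence in the article names a between-arm difference or a confidence interval for a treatment effect. Nothing is said about what is reported when the interaction is not significant.

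The same section also plans, without any condition, simple tests: "Between-group comparisons were performed using the independent-samples t-test or Mann–Whitney U test, as appropriate". The descriptive form is fixed too: "Normally distributed data are presented as mean ± standard deviation (SD"), or median and interquartile range otherwise. No estimated difference or interval is attached to these. On testing it adds "All statistical tests were two-sided", with 0.05 as the threshold.

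**The concern.** Estimation is tied to a test result. The rule applies to all repeated-measures data and so includes the primary outcome. Two consequences follow.

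- If the interaction is not significant, the plan provides no covariate-adjusted between-arm estimate and no interval. The reader gets a p-value from the model, a summary for each arm and an unadjusted test. The main model then says nothing about how large a benefit remains compatible with the data.
- If the interaction is significant, the reported LSMD has passed a filter that favours large observed differences. On average it overstates the true effect.

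The Discussion warns that the sham procedure may be active and that differences between groups may be attenuated. The authors thus foresee a small difference, and that is the case in which the filter most often blocks the estimate and most distorts it. The sample size section states that only the primary endpoint was powered, so the secondary outcomes are exposed as well.

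**Working it through.** **The plan's own figure.** Inputs from Sample size calculation: means 8.79 and 12.36, SDs 4.63 and 4.26, two-sided α 0.05, power 80%, dropout 20%.

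- Difference: 12.36 − 8.79 = 3.57.
- Pooled SD: √((4.63² + 4.26²)/2) = 4.449. Standardised difference: 3.57/4.449 = 0.80.
- Two-sample t-test (noncentral t): 26 per arm, power 0.810.
- Dropout: 26/(1 − 0.20) = 32.5, rounded up to 33 per arm, 66 in total. This matches the plan.

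**The filter.** With three visits the interaction has 2 degrees of freedom. It asks whether the between-arm differences in change from baseline at week 4 and week 8 are both zero. With complete data and an unstructured covariance this is Hotelling's T² on the two change scores, with F = (v − 1)/(2v) × T², v = 2n − 2 = 50, on 2 and 49 degrees of freedom. Each setting used 20,000 simulated trials.

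Assumptions not in the documents: equal correlation between visits of 0.3, 0.5 or 0.7; no baseline difference; the same effect at weeks 4 and 8; 26 completers per arm; no covariates. The effect of 1.8 points is about half the planned one.

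| True effect | Visit correlation | Interaction not significant, so no LSMD | Mean week-4 LSMD when reported | Excess |
|---|---|---|---|---|
| 3.57 | 0.3 | 31% | 3.77 | 6% |
| 3.57 | 0.5 | 16% | 3.66 | 3% |
| 3.57 | 0.7 | 3% | 3.59 | 1% |
| 1.8 | 0.3 | 78% | 2.29 | 27% |
| 1.8 | 0.5 | 71% | 2.18 | 21% |
| 1.8 | 0.7 | 55% | 1.99 | 11% |

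Excess = mean reported LSMD / true effect − 1; for example 2.29/1.8 − 1 = 0.27. The conditional means at 1.8 points move by a few hundredths of a point between runs.

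**Sensitivity.** A separate simulation used 27 per arm, compound symmetry, a 2-df F test, and a week-8 effect either kept in full or halved.

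- At 3.57 points the interaction was not significant in about 2% to 42% of trials, and the excess was 0% to 12%.
- At 1.785 points it was not significant in about 53% to 82%, and the excess was about 12% to 48%.

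**Without the filter.** In the same simulations the week-4 difference averaged over all trials is 3.56 to 3.58 for a true 3.57. Reporting every estimate therefore removes the selection.

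**The case against.** The strongest reply has four parts.

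1. **Crude results remain available.** This is correct. Arm means, SDs and between-group tests are planned unconditionally. A reader might infer that a null outcome leaves meta-analysts with nothing usable; the document does not support that. For an outcome summarised by means, a crude difference and interval follow from SD and n. With 26 per arm the half-width is t(0.975; 50) × 4.449 × √(2/26) = 2.48 points. What is missing is the adjusted model-based estimate with its interval. A crude mean difference is also harder to recover where only medians are shown.

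2. **The 5-point threshold is no yardstick for this estimate.** Also correct. A reader might infer that the missing interval stops the trial from excluding a benefit near its own anchor. Primary outcome says "a reduction of ≥5 points from baseline in the CCS was prespecified as a threshold for clinically meaningful improvement". That is a change from baseline used to describe treatment response, not a margin for a difference between arm means. The planned difference of 3.57 is itself below 5.

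3. **The frequencies are simply one minus the power of the interaction test, they depend on an unknown correlation, and bias at the planned effect is small.** All true. At correlation 0.7 and 3.57 points the rule has almost no effect. The larger figures belong to smaller effects.

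4. **The text does not say estimates are withheld, and an article condenses the full protocol.** The final clause could be meant as a general remark on presentation. The sentence structure does not favour that reading: the opening condition governs the whole sentence, and the results it mentions are those of the post hoc comparisons. The article states a reporting rule here, so this is not a detail merely left to another document.

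**Conclusion.** The point stands as a reporting rule that is fixed badly. On its plain reading, the plan makes adjusted between-arm estimates and intervals depend on significance.

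For the primary outcome at the planned effect the cost is modest: no LSMD in about 31% to 3% of trials as the assumed correlation rises from 0.3 to 0.7, and a selection excess of about 1% to 6%. At about half the planned effect it is substantial: no LSMD in about 78% to 55%, and an excess of about 11% to 27%. These figures assume 26 completers per arm, SD 4.449, equal effects at weeks 4 and 8 and no covariates. A fading effect makes both worse.

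The sample size, the data collected and the interaction test itself are unaffected.

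**What to change.** Replace the conditional sentence in Statistical analysis, or settle it in the SAP, along these lines: between-arm LSMDs with 95% CIs at week 4 and week 8 will be estimated and reported for CCS and for every secondary outcome analysed by linear mixed model, regardless of the interaction p-value; the interaction test governs only claims of statistical significance. Bonferroni correction can stay for the post hoc p-values.

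The cost is one sentence. The models already planned supply the estimates, no new data are needed, and the total stays at 66.

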## Discussion

5

Constipation is highly prevalent among patients with PD (Knudsen et al., 2017). Accumulating evidence indicates that constipation is closely associated with both the onset and progression of PD. Patients with PD-related constipation tend to exhibit more severe motor impairment and a higher burden of non-motor symptoms. This association suggests that constipation may reflect a more advanced or widespread neurodegenerative process rather than an isolated peripheral symptom (Camacho et al., 2021). Importantly, PD-related constipation differs fundamentally from functional constipation observed in the general population. Emerging evidence suggests that PD-related constipation is partly attributable to enteric nervous system dysfunction and dopaminergic signaling alterations, resulting in impaired gastrointestinal motility that closely parallels motor dysfunction (Singaram et al., 1995). As motor symptoms worsen, reduced physical activity and increased use of antiparkinsonian medications may further aggravate constipation. In turn, impaired gastrointestinal motility can reduce intestinal drug absorption, potentially diminishing therapeutic efficacy and creating a vicious cycle.

Current therapeutic strategies for PD-related constipation primarily focus on promoting gastrointestinal motility to alleviate bowel symptoms. However, these approaches may be associated with adverse effects and generally provide limited improvement in other PD-related symptoms (Johanson and Kralstein, 2007). Acupuncture, a simple, safe, and widely accepted complementary therapy, has shown preliminary clinical efficacy in the treatment of PD-related constipation (Li et al., 2023). However, current research in this field is characterized by two major limitations. First, most randomized controlled trials have used levodopa therapy alone or levodopa combined with prokinetic agents as control interventions. Only a small proportion of studies have accounted for the potential placebo effects of acupuncture by employing sham acupuncture as a control condition. To our knowledge, no double-blind clinical randomized controlled trials investigating acupuncture for PD-related constipation have been identified in publicly available databases. This absence may partly reflect the procedural characteristics of acupuncture, for which acupuncturist blinding is inherently difficult to implement, thereby introducing a potential risk of bias. Second, most existing studies have relied primarily on subjective clinical rating scales as primary outcome measures, without incorporating objective biological markers or further exploring the underlying mechanisms of therapeutic effects. Exclusive reliance on subjective outcomes is susceptible to placebo effects, expectancy bias, and assessor bias and may obscure potential discrepancies between symptomatic improvement and the underlying pathological processes.

Against this background, the trial is designed as a high-quality randomized controlled trial to minimize the influence of placebo effects and expectancy bias, while simultaneously exploring potential mechanisms involving gut metabolic pathways. Based on prior evidence and clinical expertise, Sishen Needle and Intestinal Three-Needle (Tianshu [ST25], Guanyuan [CV4], and Shangjuxu [ST37]) were selected as the intervention acupoint sets. Both represent classic and widely applied components of Jin’s three-needle system and have demonstrated clinical relevance in the treatment of gastrointestinal dysfunction (Li et al., 2023; Li et al., 2023).

To address methodological limitations in previous acupuncture studies, this trial innovatively employs a disposable double-blind acupuncture device developed by [name] research team. Identical intervention procedures are applied in both the real and sham acupuncture groups, with the only difference being the type of needle incorporated within the device. The real and sham devices are indistinguishable in appearance, and an embedded friction mechanism simulates tissue resistance during needle insertion, preventing acupuncturists from identifying needle type based on tactile feedback or visual cues. Furthermore, the sham needles are precisely engineered with controlled length and a smooth blunt tip, allowing participants to perceive mild pricking sensations without actual skin penetration. This design supports a double-blind approach in acupuncture trials and may help reduce subjective bias from both practitioners and outcome assessors while improving the rigor of placebo-controlled evaluation. However, it must be acknowledged that both real and sham acupuncture interventions may induce nonspecific physiological, placebo-related, and contextual effects, which should be considered when interpreting the results. As a consequence, between-group differences may be attenuated, and observed effects may not fully reflect the specific effects of acupuncture. Despite this limitation, the trial is expected to provide a more objective assessment of both the clinical efficacy and the associated biological changes of acupuncture in PD-related constipation. In addition, clinical biofluid samples are incorporated to capture objective biological responses to treatment. Given the central role of the gut in PD pathogenesis, fecal samples are collected to reflect gut microbial function associated with constipation. SCFAs, HDAC1, and pS129-*α*-syn are measured to evaluate changes in microbial metabolism, epigenetic regulation, and local pathological α-syn. Peripheral blood samples are simultaneously analyzed for HDAC1 and pS129-α-syn to explore potential systemic biomarker changes associated with acupuncture intervention.

Since early reports in 2015 linking PD to gut microbiota dysbiosis, accumulating evidence has highlighted microbial alterations and their potential contribution to disease pathophysiology (Scheperjans et al., 2015). The pathogenesis of PD-related constipation is increasingly studied within the framework of the microbiota–gut–brain axis. SCFAs, as the key microbial-derived metabolites, have consequently emerged as potential regulatory mediators in this context (Reichardt et al., 2018). Patients with PD-related constipation exhibit a reduced abundance of SCFAs-producing bacterial taxa, accompanied by decreased fecal SCFAs concentrations, indicating disruption of the intestinal microbial ecosystem (Xiao et al., 2022). SCFAs, particularly butyrate and propionate, regulate intestinal immune homeostasis in part through inhibition of histone deacetylases (HDACs), thereby modulating gene expression (Chiang and Lin, 2019). A reduction in SCFA availability has been proposed to be associated with increased HDAC1 activity, which may influence epigenetic regulation and is thought to promote pro-inflammatory responses. Disease severity in PD has been reported to correlate negatively with fecal SCFAs levels and positively with HDAC1 activity, supporting a potential link between microbial metabolic dysfunction and disease progression (Shin et al., 2020; Eshleman et al., 2024; Diniz et al., 2025). Intestinal inflammation and increased gut permeability may enhance host exposure to microbial antigens and endotoxins, thereby promoting persistent low-grade systemic inflammation (Sampson et al., 2016; Clairembault et al., 2015). Such inflammatory signaling is thought to facilitate pathological post-translational modifications of *α*-syn, particularly pS129-α-syn (Reimer et al., 2018). Studies have shown that up to 90% of α-syn in Lewy bodies in the brains of patients with PD is pS129-*α*-syn. Compared with other α-syn species, pS129-α-syn has been reported to exhibit greater propagation potential in biological environments (Ma et al., 2016). These findings suggest a potential association between gut-derived inflammatory processes and α-syn-related pathology in PD. However, the precise relationship between these pathways and neurodegenerative progression remains incompletely understood. Accordingly, this randomized double-blind controlled trial collects fecal and blood samples to quantify changes in SCFAs, HDAC1, and pS129-α-syn following acupuncture intervention in patients with PD-related constipation. These biomarker analyses are exploratory in nature and are intended to provide preliminary observational evidence regarding potential microbiota–gut–brain axis–related changes associated with acupuncture intervention. Given the limited sample size and exploratory design of this trial, causal relationships between biomarker alterations and clinical outcomes cannot be established. Accordingly, these findings warrant further investigation in larger, well-designed studies to validate these exploratory observations.

Furthermore, several limitations of this trial should be acknowledged. First, this is a single-center study recruiting patients with PD-related constipation primarily from southern China, with a relatively modest sample size. Consequently, the findings may have limited generalizability to advanced PD populations, different ethnic groups, and non-Chinese healthcare settings. Future multicenter studies incorporating more diverse demographic cohorts and disease stages are warranted to improve the external validity of the findings. Second, the 4-week follow-up period may be insufficient to fully characterize the long-term and sustained effects of acupuncture in this patient population. Therefore, future studies should incorporate longer follow-up durations and additional assessment time points to better evaluate the durability of treatment effects. Third, although SCFA levels are assessed to explore gut–brain axis–related metabolic changes, concurrent microbiome profiling is not included in the current analysis framework. We acknowledge that this may limit the depth of mechanistic interpretation of SCFA-related findings. Finally, the potential for experienced acupuncturists to become unblinded over the course of prolonged treatment remains a limitation. Further refinement of sham acupuncture devices may help improve blinding integrity in future trials.

Given the relatively high frequency of trial visits, all participants will receive standardized Mediterranean diet counseling, regular assessments of PD status, and appropriate rescue treatment for constipation when clinically indicated throughout the trial period. Upon completion of the 8-week trial, participants allocated to the sham acupuncture group will be offered up to 12 sessions of real acupuncture treatment voluntarily as post-trial compensation.
